The following drawbacks extended barrier precautions exist. First, glove use can be a key barrier to appropriate hand hygiene (14, 15). In a recent feasibility trial involving 750 infants, Khan et al. (16) found higher hand hygiene compliance rates in standard care time periods as compared to glove use periods at different moments of care: before patient contact or clean procedures as well as after body fluid or direct patient contact. Glove use may therefore confer a false sense of security, as pathogens easily contaminate gloves without performing

hand hygiene properly. Second, our cohort studies demonstrated an overuse of reserve antibiotics such as carbapenems (3, 17) associated with implementation of the weekly colonization screening in Germany. Third, extended hygiene measures are time and cost-intensive and may interfere with other priorities of neurodevelopmental support and family-centered care, e.g. avoidance of co-bedding or skin-to-skin contact of twins with different screening results. Fourth, disposable gloves are the most commonly used single-use item in intensive care. Their production requires natural resources, and they significantly contribute to hospital waste (18). To our best knowledge, there is no evidence on particular benefits on the use of gowns in the care of NICU patients (19).

In the BALTIC trial following hypothesis will be tested:

The care of NICU-treated infants with 2MRGN colonization with standard infection prevention and control strategies (IPC) alone (intervention) is not inferior to standard hand hygiene combined with the use of protective gowns and single-use gloves (control) in terms of the rate of HA infections caused by with Gram-negative pathogens (primary endpoint).

The BALTIC trial can add new data to current uncertainties. The multi-center network structure may generate population-representative data on the prevalence of MRGN in German NICUs. BALTIC also provides the basis for implementing a multi-center antimicrobial stewardship program. We also aim to evaluate the costs of extended hygiene measures given the increased consumption of disposable items.

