### *Outcomes*

The primary endpoint is the rate of HA bloodstream infections with Gram-negative pathogens in all preterm and newborn infants who received colonization screening. This outcome is defined clinically according to NEO-KISS criteria (at least two clinical signs of sepsis + one laboratory sign, e.g. increase in C-reactive protein > 10mg/l) after 72 hours of life and requires the detection of a Gram-negative pathogen in the blood culture. Blood-culture isolates will be sent from the study centers to the study management.

Key secondary endpoint is the 2MRGN transmission rate which is assumed if another infant is colonized with the same 2MRGN pathogen after 2MRGN colonization or infection of an infant

requiring intensive care in a temporal (maximum 90 days) and spatial context (potential contact in the intensive care unit) (26). This assumption is made if, in addition to pathogen identification, the antimicrobial susceptibility testing patterns are identical. Suspected transmission of or bloodstream infection with an 2MRGN pathogen will be reported to the study management as severe adverse event within 24 hours.

Transmission/outbreak management remains the responsibility of the local interdisciplinary infection control team and is carried out according to local standards, including the decision whether to initiate genetic identity testing in the acute situation. 2MRGN isolates will be shipped from local sites and molecular typing will be performed at the Department of Infectious Diseases and Medical Microbiology at the University of Lübeck. Other secondary outcomes at the level of study sites per period ("study phase") are:

- Rate of clinical and culture proven infections
- Rate of infection outbreaks
- Number of initiated antibiotic cycles
- Duration of antibiotic treatment (days)
- Exposure to reserve antibiotics, including Carbapenems per study site in % infants.

To assure documentation of relevant outcomes, intensive interdisciplinary collaboration (neonatology/infectiology/hygiene/pharmacy/management) is required. Data are collected by monthly cluster report forms on infection and transmission rates and yearly surveillance of antibiotic use, disinfectant consumption, and cost estimations.

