#### *Sample size calculation and statistical analysis*

GNN and PRIMAL centers treat on average 150 preterm and critically ill neonates per year with compulsory colonization screening. The center-specific rates of Gram-negative HA infection ranges between 1.5 and 6%. Based on single center data as described above and other cohort studies (20-22) we expect 10% of these infants to be colonized with 2MRGN during hospital stay, i.e. 180 infants per 12 months observational period.

Based on previous data, we assume an intracluster correlation of maximally 0.01. Given that the observed correlation is very low, the time lag between the two trial periods is long and different patients are included in the two trial periods at each site. No carry-over effects are assumed, as we are not expecting that effects of one treatment period would influence the second period (after cross-over) since medical care-givers are aware of the study period they are in. Data from two periods at one site are regarded as two independent sites. We further assume a frequency of Gram-negative HA infections in the controls of 3% and a non-inferiority limit of 5%. Striving for a power of 0.8 ( $1-\beta$ ) with a one-sided significance level  $\alpha$  of 0.05, at least  $n=18$  patients per site and phase are required for analysis with 12 sites, thus  $n=432$  in total. To allow for a maximal drop-out of 10% drop-out, at least 480 patients need to be included.

The primary data analysis will be performed according to the intention-to-treat principle (non-linear mixed effect regression models, logit link). Generalized estimating equations are performed to determine the infection rates between the two regimens. Secondary endpoints are analysed as the primary endpoint per individual or per cluster.

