## 5 Database

The database is the data taken over from the clinical project management team according to Chapter 3. In this, data is documented entirely on an aggregated level, i.e., per month per site.

The data is structured as follows:

- Every of the 12 sites participates in the study in two phases, in one of which hand disinfection alone (IV), in the other hand disinfection plus gloves and gowns is applied (CO). The order of the two phases is randomized.
- Every phase has a duration of 12 months, so that for every site, data is collected for 24 months.
- Each of the two phases at one site is considered one cluster.
- Given the aggregation of the data in months, the observational unit is the month (month-level variables).
- Some variables give the count of patients with a specific event. From this and the number of admissions in that month, the number of patients without the specific events is constructed as well as data on patient-level is constructed for analyses (patient-level variables).

To obtain the count of patients without a specific event, the number of events is subtracted from the number of admissions [Aufnahmen\_Neo] rendering the following additional variables:

| Count of patients with the event
(original variable) | Count of patients without the event
(constructed variable) |
|---------------------------------------------------------|---------------------------------------------------------------|
| Anzahl_gramNeg_nurLOS                                   | Anzahl_gramNeg_nurLOS_negativ                                 |
| Transm_Patient                                          | Transm_Patient_negativ                                        |
| Transmission_2MRGN_Patient_SAE                          | Transmission_2MRGN_Patient_SAE_negativ                        |
| Anzahl_kl_Sepsis_allg                                   | Anzahl_kl_Sepsis_allg_negativ                                 |
| Anzahl_BKpos_Sepsis_allg                                | Anzahl_BKpos_Sepsis_allg_negativ                              |
| Anzahl_2MRGN_LOS                                        | Anzahl_2MRGN_LOS_negativ                                      |

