To allow for patient-level description, the data set is re-structured to contain one line per patient based on the documented number of patients admitted to the site [Aufnahmen\_Neo]. In this, the following month-level variables are used to construct the following patient-level variables indicating presence or absence of the event:

| Variable                                     | Month-level
(original variable) | Patient-level
(constructed variable) |
|----------------------------------------------|------------------------------------|-----------------------------------------|
| Gram negative infection                      | Anzahl_gramNeg_nurLOS              | gramNeg_nurLOS                          |
| At least one suspected transmission          | Transm_Patient                     | Transm                                  |
| At least one suspected transmission of 2MRGN | Transmission_2MRGN_Patient_SAE     | Transm2m                                |
| Clinical infection                           | Anzahl_kl_Sepsis_allg              | Sepsis                                  |
| Any BSI                                      | Anzahl_BKpos_Sepsis_allg           | Sepsis_pos                              |
| 2MRGN BSI                                    | Anzahl_2MRGN_LOS                   | LOS                                     |

For the estimation of the GEE models, a cluster variable [Cluster] is created that combines the information from the site identifier [Klinik\_ID] with the variable indicating the phase [Randomisierung], so that every site corresponds to two clusters, one for every phase.

The variable counting the number started reserve antibiotics in a month [Anzahl\_beg\_Reserve\_ATB] is dichotomized to indicate whether at least one treatment with a reserve antibiotic was started or not [Beg\_Reserve\_ATB].

In addition, the clinical project management team surveys the participating sites about consumption of disinfectant and estimated costs. This data will separately be transferred to the IMBS for analysis.

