## 9.4 Analysis of Secondary Outcome Variables

### 9.4.1 Efficacy Outcome Variables on the level of months

For the following binary variables, the observational unit is the month:

- At least one suspected transmission of 2MRGN [Transm\_2MRGN\_j\_n]
- At least one of any relevant transmissions [Transmission\_j\_n]
- At least one started reserve antibiotic [Beg\_Reserve\_ATB]

For these, the below analyses are performed:

|                            |                                                                                                                                                                                                                                                                                                                                                                                                                                                                                                                                                                                                                                                                                                                                                                                                        |
|----------------------------|--------------------------------------------------------------------------------------------------------------------------------------------------------------------------------------------------------------------------------------------------------------------------------------------------------------------------------------------------------------------------------------------------------------------------------------------------------------------------------------------------------------------------------------------------------------------------------------------------------------------------------------------------------------------------------------------------------------------------------------------------------------------------------------------------------|

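### The SAP replaces the protocol's percentage of infants exposed to reserve antibiotics with a monthly yes/no, which is a different quantity and discards information from a count already collected

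*Combined protocol and SAP*

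**What the plan says.** The protocol's Outcomes section lists, among the secondary outcomes at the level of sites per study phase: "Exposure to reserve antibiotics, including Carbapenems per study site in % infants".

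SAP section 5 describes what is held in the database: "The variable counting the number started reserve antibiotics in a month", named `Anzahl_beg_Reserve_ATB`. That variable "is dichotomized to indicate whether at least one treatment with a reserve antibiotic was started or not", which gives `Beg_Reserve_ATB`. The same section has monthly admissions (`Aufnahmen_Neo`) and uses them to rebuild patient-level data for other endpoints: "the data set is re-structured to contain one line per patient based on the documented number of patients admitted to the site".

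SAP section 9.4.1 then lists "At least one started reserve antibiotic" as a binary month-level outcome. It is analysed by an identity-link GEE with treatment as the only term, giving a risk difference between months. The section sets no hypothesis and marks the analysis as descriptive. The secondary endpoint list in SAP 4.1 has the same yes/no form. Neither the count nor a rate per infant or per admission is analysed anywhere in the SAP, and no reason is given for leaving the protocol's definition.

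**The concern.** The share of months with at least one start answers a different question from the share of infants exposed. It cannot tell a reader how many infants received a reserve drug, which is what the protocol set out to report. A month with one start and a month with six count the same.

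The SAP is also uneven here. Total antibiotic starts (`Anzahl_beg_ATB`) stay a quantity in section 9.4.1, and infections and transmissions are set against admissions in section 9.4.2. Of the two counts of antibiotic starts, only the reserve count is cut to yes/no.

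Reserve-antibiotic use is part of the trial's rationale: the protocol says that "our cohort studies demonstrated an overuse of reserve antibiotics such as carbapenems" and lists this among the drawbacks of the present approach. A measure that responds weakly to the amount of use adds little to that side of the balance.

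**Working it through.** **Plan's own figure.** There is none for this endpoint. The sample size in the protocol and SAP concerns the primary endpoint only, and the documents give no reserve-antibiotic rate. The exposed share p is therefore an assumption, shown over a range.

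**Inputs.**
- Infants per site: "GNN and PRIMAL centers treat on average 150 preterm and critically ill neonates per year with compulsory colonization screening" (protocol, sample size section), so N = 150/12 = 12.5 per site-month. This takes `Aufnahmen_Neo` to be of that order.
- Months: "Every phase has a duration of 12 months, so that for every site, data is collected for 24 months" (SAP 5). With 12 sites this is 12 × 24 = 288 site-months, or 144 per arm, and 144 × 12.5 = 1,800 infants per arm.
- p: assumed, 3% to 30%. Two figures in the protocol serve as reference points only, since neither measures reserve use: 3% is the assumed Gram-negative infection rate in controls, and 14.7% is the MRGN colonization share in the single-center cohort.

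**Formulas.** Treat the number of exposed infants in a month as binomial(N, p), and let q = (1 − p)^N.
- Share of positive months = 1 − q.
- Information on p kept by the yes/no value, relative to the count = N·p·q / [(1 − p)(1 − q)].

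Example at p = 10%: q = 0.9^12.5 = 0.268. The share of positive months is 0.732, and the information kept is 12.5 × 0.10 × 0.268 / (0.90 × 0.732) = 0.51.

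| p | positive months | information kept |
|---|---|---|
| 3% | 32% | 83% |
| 5% | 47% | 73% |
| 10% | 73% | 51% |
| 14.7% | 86% | 34% |
| 20% | 94% | 20% |
| 30% | 99% | 6% |

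**Thresholds at N = 12.5.** Half of the information is lost at p ≈ 10.2%. Ninety per cent of months are positive at p = 1 − 0.1^(1/12.5) ≈ 16.8%.

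**Unit size.** At the same p = 10%:
- 100 infants per year: 58% of months positive, 66% of the information kept.
- 150 per year: 73% and 51%.
- 300 per year: 93% and 21%.

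**Variation between months.** Overdispersion lowers the ceiling. At p = 20%, a beta-binomial intracluster correlation of 0.05 or 0.1 gives 88% or 83% positive months, against 94% without it.

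**Illustrative power for a 1.5-fold difference** (two-sided 0.05, clustering ignored), comparing 144 yes/no months with 1,800 infants per arm:

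| p | yes/no | % of infants |
|---|---|---|
| 3% | 0.56 | 0.66 |
| 5% | 0.72 | 0.87 |
| 10% | 0.83 | >0.99 |
| 14.7% | 0.78 | >0.99 |
| 20% | 0.62 | >0.99 |
| 30% | 0.22 | >0.99 |

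These figures show direction and relative size. They are not a power claim for the trial, which plans no test here.

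**The case against.** The strongest reply is that the size of the loss rests on an unknown rate. A reader might infer that most of the information is lost and that the endpoint sits near its ceiling. The documents do not support either as a general statement. At 3% to 10% exposure the indicator is positive in 32% to 73% of months and keeps 83% to 51% of the information. Its response to change also varies: a rise from 5% to 10% of infants moves it by 26 points (47% to 73%), whereas a rise from 20% to 30% moves it by only 5 (94% to 99%). This stands, and the conclusion has to be conditional.

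A reader might also infer that the yes/no value mainly measures unit size and so biases the comparison. That does not follow. Admissions and exposed share both drive the probability of a positive month, and each site contributes 12 months to each arm, so stable differences in size are largely balanced. Unit size affects sensitivity and interpretation more than bias.

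Third, the stakes are limited. The analysis is descriptive, total antibiotic starts and antibiotic days are kept as quantities, and the protocol ties reserve-drug overuse to weekly screening, which continues in both arms. This stands, although neither of those two measures is specific to reserve drugs.

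Fourth, the protocol's percentage cannot be recovered exactly, because the variable counts starts and not infants. This also stands and limits the remedy. It does not justify discarding the count.

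**Conclusion.** The point holds in a limited form. Without explanation, the SAP analyses a quantity other than the one the protocol defines, and the yes/no value carries less information than the count at every exposure rate examined. Under independent exposures and 12.5 admissions per site-month, the loss is about 17% of the information at 3% exposure, about half at 10%, and 80% or more from 20% upward. More than 90% of months are positive only above about 17%. Larger units reach these points at lower rates, and variation between months lowers the ceiling.

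The mismatch between the two definitions needs no assumption about the rate; the size of the loss does. The primary analysis is not affected. This is a worthwhile correction to a secondary, descriptive endpoint, and not a threat to the trial's main conclusion.

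**What to change.** In SAP 9.4.1, analyse `Anzahl_beg_Reserve_ATB` by a log-link Poisson GEE with treatment as the only term, offset log(`Aufnahmen_Neo`), robust standard errors and the existing `Cluster` variable. Report starts per 100 admissions by arm, with a 95% confidence interval. Months with no starts cause no difficulty in this model. Keep the monthly yes/no as a supplementary line.

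Do not use the paired events and non-events model of section 9.4.2 here. The variable counts treatment starts, so subtracting it from admissions does not give the number of unexposed infants and could be negative. SAP 8.2 has no plausibility rule for this variable.

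State in the SAP that the measure departs from the protocol's percentage of infants, and why. Starts may come from infants admitted in earlier months (median stay in the single-center cohort was 63 days) or may be repeated in one infant, so starts per admission is an approximation and should be labelled as such.

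The cost is SAP wording only. The count and the admissions are already in the database, and no new data are needed.

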## 5.1 Incomplete Treatments, Drop-Outs, and Incomplete Observations

Data is documented entirely on an aggregated level, i.e., per month per site. Therefore, there is no documentation on missing data on the individual level. Missing entries at the aggregated level are possible, and for every analysis, the number of valid entries will be clearly stated.

Reporting and visualization comply with the CONSORT guideline in its current version.

## 5.2 Protocol Deviations

For every month, the percentage of patients with 2MRGN infection who are not treated according to randomization is documented [Nicht\_nach\_Rando\_Proz] and reported.

No further protocol deviations are recorded.

## 6 Analysis Timing

No interim analyses are planned. The final analysis is performed after database closure and export to the IMBS.

## 7 Sets of Patients

Inclusion and exclusion criteria are described in detail in the study protocol both on patient- and site-level.

All analyses are performed on the intention-to-treat (ITT) analysis set that comprises patients and months from all randomized sites.

## 8 Handling of Missing Values, Missing Data, and Outliers

### 8.1 Missing Values, and Missing Data

Missing values are assumed to occur at random. Given the nature of the aggregated data, no imputation of missing entries is performed, and all analyses are based on complete case sets.

### 8.2 Outliers and implausible entries

Outliers and implausible entries are identified and, if required, corrected by the clinical project management. In addition to that, entries for the respective month are deleted if the count of patients with a specific event exceeds the count of patients, i.e., if for any month

- Transm\_Patient > Aufnahmen\_Neo
- Transmission\_2MRGN\_Patient\_SAE > Aufnahmen\_Neo
- Anzahl\_kl\_Sepsis\_allg > Aufnahmen\_Neo
- Anzahl\_BKpos\_Sepsis\_allg > Aufnahmen\_Neo
- Anzahl\_2MRGN\_LOS > Aufnahmen\_Neo

In addition, values in the respective variables are deleted if

- the count of days with blocked beds in a month [Tage\_Bettensperrung] exceeds 31 or
- the percentage of days with antibiotics treatment per patient days [ATB\_Tage\_pro\_Patiententag] < 0.

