### **Benchmarking by analysing single center data**

For the design of the Cluster-RCT we evaluated single center data of routine colonization screening (1x/week rectal swab and pharyngeal swab) from VLBWI born between January 1st, 2013 until December 31st, 2017 (n=319 infants, summarized in table 1).

*Table 1 Clinical characteristics of single center cohort of very-low-birth weight infants*

| Clinical parameter                         | cohort
n = 319 |
|--------------------------------------------|-------------------|
| Sex, female, n (%)                         | 160 (51)          |
| Multiple birth, n (%)                      | 114 (36)          |
| Gestational age, wk, median (IQR)          | 28,5 (4,1)        |
| Birth weight, g, median (IQR)              | 1091 (564)        |
| Mode of birth, n (%)                       |                   |
| Spontaneous                                | 20 (6)            |
| Elective casearean                         | 256 (80)          |
| Emergency Caesarean                        | 43 (14)           |
| Cause of preterm birth, n (%)              |                   |
| Preterm labor                              | 194 (44)          |
| Multiple causes possible                   |                   |
| Pre-eclampsia                              | 39 (9)            |
| Pathological Doppler                       | 112 (25)          |
| Placental abruption                        | 4 (1)             |
| Intrauterine growth restriction            | 63 (20)           |
| Suspected or proven amniotic infection     | 144 (45)          |
| Duration hospital stay, days, median (IQR) | 63 (41)           |
| Antibiotic days/100 days, median (IQR)     | 13,1 (14,9)       |
| Probiotic use, n (%)                       | 174 (55)          |

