Out of 319 infants, 47 (14.7%) were colonized with an MRGN pathogen, of which 30 infants (9.3%) tested positive for a 2MRGN pathogen. One infant was colonized with 2MRGN *E. coli* at birth, 15 infants were colonized within the first 5 weeks of life (figure 1). The 2MRGN pathogens were isolated from pharyngeal swabs (n=12), rectal swabs or fecal samples (n=19) or conjunctiva (n=1). Four infants were colonized with > 1 MDRO including two infants with MRSA and 3MRGN *E.coli* and two infants with 2MRGN *Enterobacter cloacae* and either 2MRGN *E.coli* or 2MRGN *Klebsiella pneumoniae*. Colonization with 2MRGN occurred at a median of 33 days. Figure 1 describes the timepoint of first colonization with MDRO in vulnerable infants. Seven infants were initially colonized with antibiotic susceptible bacteria and acquired 2MRGN features during hospital stay.

Out of 319 of infants, 296 received antibiotic therapy for a median duration of 7 days, 252 infants were already started on antibiotics on day 1 of life. MDRO colonized infants were treated for a median of 7 days. Among 2MRGN colonized infants, one infant developed a 2MRGN *E.coli* sepsis on day 6 of life, two infants were diagnosed with 2MRGN sepsis (*Enterobacter* spp.) between day 7 and 28 of life and five infants were treated for culture-negative sepsis. Our data are in line with previous single center studies in Germany with evidence of MDRO colonizing infants in 4.9% of 635 neonates, 12.7% of 584 screened neonates and 15.3% of 1407 preterm infants, respectively (20-22). In a recent multicenter RCT on the effect of probiotics to prevent MDRO colonization in preterm infants 28-32 weeks of gestation, we confirmed center-specific MDRO colonizing rates between 5-20% (23). In the BALTIC trial, we therefore estimated the number of 2MRGN colonized infants to be 10% during the hospital stay.

[figure not shown]

**Figure 1:** First detection of MRGN, MRSA, MRSA or Vancomycin resistant enterococci (VRE)

MRDO = Multi-drug resistant organisms; KRINKO = German Commission on Hospital Hygiene and Infection Prevention, MRGN = Multidrug-resistant Gram negative bacteria, 2MRGN (resistant to Piperacillin and Cefotaxim or Ceftazidim), 3MRGN (resistant to Piperacillin and Cefotaxim or Ceftazidim and fluorquinolones), MRSA = methicillin-resistant *Staphylococcus aureus*, VRE = Vancomycin resistant *Enterococci*

Additional first detections after the 15th week of life: n = 4 2MRGN pathogens

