### 9.3 Analysis of Primary Outcome Variables

Based on previous data, we assume a correlation within sites and phases of maximally 0.01. Given that the previously observed correlation is very low, the time lag between the two trial phases is long and different patients are included in the two trial phases at each site, no carry-over effects are assumed. We thus are not expecting that effects of one treatment phase would influence the second period after cross-over, so that data from two phases at one site are regarded as independent.

For the primary analysis, we estimate a GEE model, taking a possible correlation within the phases at one site (cluster as defined above) into account. Assuming a very low intra-cluster correlation, we use the independence structure for the working correlation. To obtain an estimate of the risk difference, an identity link is used. To test for non-inferiority, a margin of 0.05 has been defined.

|                         |                                                                                                                                         |
|-------------------------|-----------------------------------------------------------------------------------------------------------------------------------------|
| Outcome variable        | Anzahl_gramNeg_nurLOS, Anzahl_gramNeg_nurLOS_negativ                                                                                    |
| Endpoint                | Gram-negative BSI                                                                                                                       |
| Effect measure          | Risk difference                                                                                                                         |
| Primary Estimand |                                                                                                                                         |
| Population              | Newborns requiring intensive care in one of the participating NICUs undergoing KRINKO screening and being treated with hygiene measures |
| Treatment               | Standard hygiene measures (hand disinfection plus gloves and gowns, CO) versus hand disinfection only (IV)                              |
| Hypothesis              | Non-inferiority, i.e.
$H_0$ : Risk for gram-negative BSI in IV – Risk for gram-negative BSI in CO group $\geq 0.05$                  |

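### SAP 8.2 deletes months in which events exceed that month's admissions, although such counts can be genuine, and it leaves the handling of the primary count unclear

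*Combined protocol and SAP*

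**What the plan says.** SAP section 5 describes the database as aggregated by month and site. For each of six event counts, patients without the event are constructed by subtraction: "the number of events is subtracted from the number of admissions". The six counts are Gram-negative late-onset infection (the primary variable, Anzahl_gramNeg_nurLOS), any transmission, 2MRGN transmission, clinical sepsis, culture-positive sepsis and 2MRGN BSI.

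SAP section 8.2 first has the clinical project management find and correct implausible values. As a further step, "entries for the respective month are deleted if the count of patients with a specific event exceeds the count of patients". Five comparisons with Aufnahmen_Neo (admissions) follow. They cover every count except Anzahl_gramNeg_nurLOS, from which section 9.3 analyses the primary endpoint, "Gram-negative BSI".

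Section 8.1 says "Missing values are assumed to occur at random" and restricts analyses to complete cases, without imputation. Section 7 defines the ITT set as patients and months from all randomized sites. No analysis that retains the deleted months is planned.

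**The concern.** The rule treats events above admissions as impossible. That would be so only if every event in a month belonged to an infant admitted in the same month, and nothing in the documents says this. The protocol's own figures point the other way. Table 1 gives a median stay of 63 days (IQR 41) in one centre's very-low-birth-weight cohort. In the same cohort, "Colonization with 2MRGN occurred at a median of 33 days". The protocol's Outcomes section allows up to 90 days between the infants linked in a suspected transmission.

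If such a month is genuine, deletion discards real events because of their number. The loss then depends on the outcome, which is what the missing-at-random assumption excludes. At stake are mainly the endpoints on which barrier care would be expected to act, including 2MRGN transmission, the protocol's key secondary endpoint.

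The primary variable raises a separate question, because it is absent from the list and the scope of deletion is not stated.

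**Working it through.** The plan gives no figure for how often the rule will apply, so there is none to reproduce.

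**Inputs from the documents**
- Admissions: "GNN and PRIMAL centers treat on average 150 preterm and critically ill neonates per year" (protocol, Sample size calculation). This gives 150/12 = 12.5 per site and month. As a check that 150 is per centre, 12 × 150 × 10% = 180, the protocol's own yearly number of colonized infants.
- Primary risk: 3% in controls; centre range 1.5 to 6%.
- Any BSI in very-low-birth-weight infants: 10 to 20% (protocol, Background).
- Site-months: 12 sites × 24 months = 288.

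**Assumptions**
- Stays of 14 and 21 days as alternatives to 63, because the documents give no stay for the other critically ill newborns.
- The 10 to 20% rate is also used for transmission, for which no rate is stated.
- Poisson admissions. Events are either Poisson or clustered (negative binomial, k = 0.2, variance m + m²/0.2 for mean m).
- 5 admissions a month for a small site.

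**Step 1: can events exceed admissions?** Infants present at some time in a month = admissions × (stay + 30.4)/30.4.

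| Stay (days) | Infants present in month | Ratio to 12.5 admissions |
|---|---|---|
| 14 (assumed) | 18.3 | 1.46 |
| 21 (assumed) | 21.1 | 1.69 |
| 63 (Table 1) | 38.4 | 3.07 |

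At each of these stays more infants are present than are admitted. Of the two, only a count above the infants present would be impossible.

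**Step 2: direction.** Take an arm with Y events in N admissions, Y/N < 1. A deleted month has y > n, so y/n > 1 > Y/N, and (Y − y)/(N − n) < Y/N. For the triggering variable the arm's estimated risk can only fall.

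**Step 3: how often.** Expected months out of 288 with events above admissions:

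| Admissions per month | Event risk | Poisson | Clustered |
|---|---|---|---|
| 12.5 | 3% | 0.002 | 0.20 |
| 12.5 | 6% | 0.01 | 1.6 |
| 12.5 | 10–20% | 0.05–0.5 | 5–17 |
| 5 | 3% | 0.4 | 0.95 |
| 5 | 10–20% | 2–7 | 7–18 |

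The rows for 5 admissions treat all sites as small, so they are an upper scenario.

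**Step 4: size if it happens.** Take an arm of 12 × 150 = 1,800 admissions with a 3% risk outside the affected months.
- One month with 15 events on 12 admissions: (0.03 × 1,788 + 15)/1,800 = 3.81%. Deletion returns 3.00%, a loss of 0.81 points.
- One small-site month with 4 events on 3 admissions: (0.03 × 1,797 + 4)/1,800 = 3.22%, a loss of 0.22 points.

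These months are illustrations, not predictions.

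**Step 5: the primary count.** Section 8.2 speaks of the month's entries for this rule. For its next rule, on blocked beds and antibiotic days, it speaks of values in the variables concerned. Two readings are open.
- *Whole row deleted.* An excess in another count removes the primary data for that month, and also month-level outcomes that need no admissions denominator. The direction of that effect on the primary risk is not fixed.
- *Only the triggering variable deleted.* A primary count above admissions stays in, its non-event count is negative, the binomial model in section 9.3 cannot use it, and no instruction is given.

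**Step 6: do totals change the estimate?** Under independence with only the phase variable in the model, each risk is ΣY/ΣN. Its robust variance is Σ_c(Y_c − N_c p)²/N², where c is the SAP's site-by-phase cluster. Both depend on cluster sums only. A numerical check on simulated data gave the same risk difference and robust SE from 288 monthly rows as from 24 totals.

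**The case against.** The best defence is that the rule will almost never touch the primary result. At 3% and 12.5 admissions a month this is correct. The larger counts for other endpoints depend on an assumed degree of clustering, and the SAP labels those endpoints descriptive. Section 8.2 also has a correction step before deletion, and section 5.1 promises the number of valid entries for each analysis. All of this stands and limits the weight of the point. It does not remove it: deletion is applied on top of the correction step, no provision keeps a value that the site confirms, and a count of valid entries does not show deletions by arm and reason.

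Three stronger readings are tempting, and the documents do not support them.
- *The rule hides primary events and favours non-inferiority.* If deletion is by variable, no primary count is deleted, because that count is not listed. If it is by row, primary data can be lost, but the expected number of months is small for the primary count itself. Which arm would lose more is unknown in either case.
- *Infants at risk far outnumber admissions.* The 63-day stay is a median from very-low-birth-weight infants at one centre, while the trial also takes other critically ill newborns. The mismatch persists at 14 to 21 days, but at about 1.5 to 1.7 rather than 3.
- *The deleted months are outbreak months with real data.* Low admissions or an entry error can also trigger the rule. The documents do not tie blocked beds to outbreaks, and they do not define the month to which an event is assigned.

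**Conclusion.** The point holds as a defect in the data-handling rule and in its wording. Events above admissions do not by themselves show an error. Automatic deletion depends on the outcome, works in one direction for the variable concerned, and contradicts section 8.1.

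For the primary endpoint the likely effect is negligible at average rates and site size (0.002 to 0.20 of 288 months). It can be material for any BSI and transmission if events cluster (5 to 17 months at an assumed 10 to 20% and k = 0.2), but is slight if they do not (0.05 to 0.5). Clinical infection shares the same rule. Small sites are more exposed.

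The conclusion assumes that events are recorded in the month they occur. This is plausible for monthly cluster reports but is not stated. The gap over the primary count does not depend on that assumption: the SAP has to say what is deleted and what happens to Anzahl_gramNeg_nurLOS. The change should be made, but nothing here shows that the primary conclusion is at risk.

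**What to change.** 1. In section 8.2, replace automatic deletion with a query to the site. Keep confirmed values. Delete only confirmed errors, and only in the variable affected.
2. Apply this to all six counts, including Anzahl_gramNeg_nurLOS.
3. Report any deletions by arm and reason.
4. For the unadjusted primary and patient-level GEE models, sum events and admissions to site-phase totals, using the SAP's own clusters. Step 6 shows that the estimate and robust SE are unchanged, and a confirmed month with events above admissions can then be kept.
5. Leave the month-level outcomes and the confounder models of section 9.3 on monthly rows, since understaffing, blocked beds and paediatric admissions vary by month. For the confounder models, state how a confirmed month with events above admissions is handled, and report how many there are.
6. Add a sensitivity analysis per patient-day only if patient-days were exported. The SAP lists the antibiotic-day ratio but not its denominator.

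The cost is a few data queries, a short aggregation step and minor rewording of the SAP. The sample size is not affected.
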